**Primary outcomes**								
	Substance use	Addiction Severity Index^b^		x			x	x
		Urine drug screen^b^		x	x	x	x	x
		Timeline Followback^b^		x	x	x	x	x
	HIV risk behavior	Reback Behavioral Risk Assessment^c^		x			x	x
	ART adherence	Unannounced pill counts^b^		x	x	x	x	x
		Viral load/CD4^b^		x			x	x
**Secondary outcomes**								
	Medication compliance	Self-report^c^		x	x	x	x	x
	Behavioral strategies	Self-report^c^		x				x
	Depression	PHQ-9^c,d^		x	x	x	x	x
	Anxiety	OASIS^c,e^		x	x	x	x	x
	Drug-taking self-efficacy	Drug-Taking Confidence Questionnaire^c^		x			x	x
	Health-related quality of life	SF-12^c,f^		x			x	x
	Readiness for change	SOCRATES-D^c,g^		x				
**Covariates**								
	Demographics	Self-report^c^	x					
	Psychiatric diagnosis	M.I.N.I. International Neuropsychiatric Interview^b^	x					
	Concomitant medications	Self-report^b^		x	x	x	x	x
	Ancillary treatments	Self-report^c^		x	x	x	x	x
**Participant satisfaction** ^a^								
	Participant satisfaction	Weekly qualitative calls^b^			x	x	x	
	Participant adherence	Message exposure^b^			x	x	x	

^a^Only for participants randomized to the TXT-CBT group.

^b^Research assistant–administered.

^c^Participants used a Web-based data entry system.

^d^Patient Health Questionnaire.

^e^Overall Anxiety Severity and Impairment Scale.

^f^Short Form Health Survey.

^g^Stages of Change Readiness and Treatment Eagerness Scale.

### Secondary Outcomes

#### Self-Reported Medication Adherence

Self-reported adherence was assessed monthly using a brief 3-item adherence survey developed by Kalichman et al [61]. Using a visual analogue rating scale, participants were asked to indicate their best guess, ranging between 0% and 100%, about how much of their HIV medication they have taken in the past week and in the past month. They were also asked how confident they were that they can take all of their HIV medications in the next week.

#### Behavioral Strategies for Adherence

From a 25-item behavioral strategies checklist developed by Kalichman et al [60], participants were asked to indicate how often they have used these strategies during the past 3 months. Answer choices are never, sometimes, often, very often, and always. Examples of strategies included in the questionnaire are “used a pill box organized by day of the week” and “used bedtime as a reminder to take medications.”

#### Depression

The Patient Health Questionnaire (PHQ-9) [62,63] is a self-administered, 9-item questionnaire used to assess depression. It includes DSM-IV depression criteria as well as other major depressive symptoms. The PHQ-9 is a reliable and valid measure of depression [62,63]. Participants were asked to report “how often they have been bothered by any of the following problems” with response choices ranging from “not at all” to “nearly every day.”

#### Anxiety

The Overall Anxiety Severity and Impairment Scale (OASIS) was used to assess severity and impairment associated with anxiety [64]. It is a 5-item measure that is valid across anxiety disorders, for multiple anxiety disorders, and with subthreshold symptoms [64]. Participants were asked to identify which answer best describes what they have been feeling in the past week. Three questions have answer choices that range from “none” to “extreme,” and two range from “none” to “constant” anxiety.

#### Drug Taking Self-Efficacy

Drug taking self-efficacy was measured using the Drug-Taking Confidence Questionnaire [65], which measures confidence in avoiding alcohol and other drugs (abstinence goal) or heavy use (moderation goal) across the 8 high-risk categories in Marlatt’s taxonomy of relapse precipitants [66]. Participants imagined themselves in 8 specific situations and rated confidence in resisting the urge to drink heavily or use a specific drug.

#### Health-Related Quality of Life

The health status questionnaire [67,68] measures mental and physical functioning as well as overall health-related quality of life. All 12 questions come from the 36-item Short Form Health Survey (SF-36) [67,68]. Participants were asked whether their daily activities are impacted as a result of their physical health or emotional problems.

#### Readiness for Change

The Stages of Change Readiness and Treatment Eagerness Scale (SOCRATES-D) is a 19-item scale used to assess readiness and motivation for change in drug users [69]. The SOCRATES instrument has 3 subscales: Recognition, Ambivalence and Taking Steps. Participants are asked to rate how much they agree or disagree with a statement “right now.” Possible answers range from “strongly disagree” to “strongly agree.” Examples of statements are “I really want to make changes in my use of drugs,” “sometimes I wonder if I am in control of my drug use,” and “I am actively doing things now to cut down or stop my use of drugs.”

### Covariates

Demographic variables, psychiatric diagnosis, ancillary treatments, and message exposure (participant adherence to TXT-CBT) were examined as potential moderating or mediating variables.

### Participant Satisfaction With TXT-CBT

Participant satisfaction with the TXT-CBT intervention was assessed using qualitative weekly phone-based interviews in which those assigned to the experimental group were asked a series of scripted questions concerning the perceived helpfulness of the intervention in that week. Participants were queried concerning any messages that stood out as particularly helpful or that they might have disliked and whether and how the intervention helped them to change behaviors in the key domains of interest (ie, ART adherence, drug use, and/or other risk behaviors).

### Statistical Analyses

Analyses in the pilot study will allow basic description of the sample in terms of distributional characteristics, variability, and missing data as well as examination of possible effect sizes in comparing the groups. Preliminary analyses will include descriptive statistics and confidence intervals, computation of scale scores, and assessment of reliability. Exploratory analyses will use a random effects regression approach to examine group differences across the repeated observations (baseline, treatment end, and follow-up) as specified in each of the study aims. This type of model accommodates the (potentially correlated) repeated measures and allows for inclusion of covariates (ie, subject characteristics on which the groups differ at admission) and additional repeated observations for some measures (eg, viral load at baseline, treatment end, and follow-up). The pilot sample size of 25 per group should allow detection of an effect size of approximately d=.7 in differential change in outcomes from baseline to follow-up, assuming a moderate correlation of 0.50 over time and allowing attrition of up to 20% (power=.80, one-tailed alpha=.05). This detectable effect size would translate to a differential change of about 19 points on the ART adherence composite score assuming an average (across time) pooled (across groups) standard deviation of about 27, as found by Safren [11] for a specialized CBT intervention for HIV-infected individuals. Safren et al found a differential change of approximately 25 points.

Separate analyses will address each measure in aims 1, 2, and 3. For example, analyses for aim 2 will include as dependent variables urine toxicology results for opioids and stimulants, ART adherence scores, health-related quality of life scores from the SF-12, and select items from the ASI indicating number of days in the past month utilizing health services. Analyses for aim 3 will include correlations between changes in self-efficacy (Drug-Taking Confidence Questionniare) and treatment retention and substance use during and after treatment.

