### Aims

This paper describes the methodology leading to the development and pilot testing of a CBT-based text messaging intervention (TXT-CBT) targeting ART adherence and drug use. Although there are features of CBT such as direct therapist feedback concerning therapy homework, for example, that cannot be replicated using a predominantly automated text messaging platform, the TXT-CBT program transports the essential features of CBT for relapse prevention to the technology-assisted platform, with recognition of these inherent limitations. Some of the limitations imposed by a technology-based approach are mitigated by the involvement of a clinician in the TXT-CBT intervention program.

The purpose of this study was to develop, with user feedback, a 12-week CBT-based text messaging treatment program targeting ART adherence and drug use and test its efficacy through a pilot randomized clinical trial. The specific aims of the study were to (1) test the impact of TXT-CBT over and above usual care for HIV on substance use and health care outcomes, (2) evaluate the differential effect of TXT-CBT versus usual HIV care on HIV risk behavior and ART adherence, and (3) examine potential mechanisms of action of TXT-CBT.

The following hypotheses addressed the goals of the study:

Among substance-dependent adults receiving HIV care, TXT-CBT would yield superior clinical outcomes relative to usual care in reducing substance use and health service utilization during and after treatment. In particular, while some health care utilization may increase among those who benefit from TXT-CBT (eg, use of routine HIV care services), we anticipate reductions in hospitalizations and emergency care services secondary to substance use.TXT-CBT would have superior effects on ART adherence and HIV risk behaviors relative to usual HIV care.TXT-CBT would have a direct effect on psychological variables that are recognized mechanisms of change in CBT treatment for addicted populations (negative affect, self-efficacy, social support). Specifically, we predicted that reductions in negative affect and cravings and increases in self-efficacy and social support would be positively associated with retention in TXT-CBT and inversely related to substance use during and after treatment.

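### The baseline-to-follow-up change contrast is valid but inefficient: on the plan's own inputs it has about 70% power, not the stated 80%, and adjusting for baseline restores about 81%

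*Protocol article*

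**What the plan says.** Statistical Analyses describes a "random effects regression approach to examine group differences across the repeated observations (baseline, treatment end, and follow-up"). Baseline is therefore one of the outcome observations. The covariates allowed there are subject characteristics on which the groups differ at admission. The section on the substance use outcome adds the Addiction Severity Index (ASI) drug severity composite as a covariate. No passage names the baseline value of each outcome as a covariate for that outcome, or fixes the arms' baseline means to be equal.

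The effect is then sized: "The pilot sample size of 25 per group should allow detection of an effect size of approximately d=.7", expressed as "differential change in outcomes from baseline to follow-up", "assuming a moderate correlation of 0.50 over time" and "allowing attrition of up to 20" per cent, with "power=.80, one-tailed alpha=.05". The hypothesis for aim 2 is directional: "TXT-CBT would have superior effects on ART adherence and HIV risk behaviors relative to usual HIV care". The Randomization section places random assignment after the baseline assessment. Table 1 lists follow-up (week 24) as a visit separate from week 12.

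**The concern.** Randomisation makes the true baseline difference between arms zero. An unconstrained change contrast still subtracts the observed baseline difference in full, so any chance imbalance enters the estimate as noise. Baseline adjustment subtracts only the part that predicts the later value.

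With about 20 completers per arm, the difference is large enough to matter. The article makes the exploration of effect sizes a purpose of the pilot (Sample Size), and it ties a larger, fully powered trial to whether the hypotheses are supported (Limitations). A noisier estimate serves that decision less well, and the stated 80% overstates what the named contrast delivers.

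**Working it through.** **Inputs from Statistical Analyses.** 25 per group; 20% attrition, so 25 × 0.80 = 20 per group; d = 0.7; correlation ρ = 0.50; one-tailed α = 0.05; stated power 0.80. The effect is in units of the cross-sectional SD: 0.7 × 27 = 18.9, the article's 19 points.

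**Assumptions added.** Equal variances and one common correlation between all visits; completers only; d = 0.7 at week 24.

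**Formula.** With unit SD, noncentrality = d / (s × √(2/n)), where s is the SD of the contrast within an arm. At n = 20, √(2/20) = 0.3162. Power is from the noncentral t distribution.

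**1. Reproducing the stated 0.80 with the named contrast, change from baseline to week 24.**
- s² = 2(1 − ρ) = 1.00, so s = 1.
- Noncentrality = 0.7 / 0.3162 = 2.21; critical t (38 df) = 1.686.
- Power = 0.702 (0.715 by the normal approximation).
- At 25 per group, with no attrition, the same contrast gives 0.787 (normal: 0.797). The named contrast therefore reaches about 0.80 only if the attrition allowance is not applied.

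**2. Week-24 contrast adjusted for baseline.**
- s² = 1 − ρ² = 0.75, so s = 0.866.
- Noncentrality = 0.7 / (0.866 × 0.3162) = 2.56; critical t (37 df) = 1.687.
- Power = 0.806 (normal: 0.819).

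**3. The same two contrasts at other correlations, 20 per group.**

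| ρ | Change to week 24 | Week 24 adjusted for baseline | Difference (points) |
|---|---|---|---|
| .30 | 58% | 74% | 16 |
| .50 | 70% | 81% | about 10 |
| .70 | 88% | 92% | 4 |

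**4. Detectable effect and sample size at 80% power, ρ = .50 (normal approximation).**
- Detectable d at 20 per group is (1.645 + 0.842) × s × 0.3162: 0.786 for change and 0.681 adjusted.
- For d = 0.7 the change contrast needs 26 completers per group, or 33 enrolled (26/0.8 = 32.5). The adjusted contrast needs 19 completers, or 24 enrolled (19/0.8 = 23.75). The planned 25 fits the adjusted contrast only.

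**The case against.** The strongest reply is that the stated 0.80 can be reproduced from a differential-change contrast after attrition. If the effect is the mean of week 12 and week 24 minus baseline, then s² = 1 + (1+ρ)/2 − 2ρ = 0.75 and power at 20 per group is 0.807. That arithmetic is right, but the article names change to follow-up and nowhere states an average of two later visits. Even on that reading the efficiency point remains: the same average adjusted for baseline has s² = (1+ρ)/2 − ρ² = 0.50 and power 0.924.

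A second reply is that adjustment is not absent, since covariates that differ at admission and the ASI drug composite are allowed. This is true, and the composite may serve as its own baseline covariate for that one measure. For the other outcomes, it does not stand in for their own baseline values. A covariate that is constant over time and enters only as a main effect also cancels out of a change contrast when the data are complete.

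Third, the analyses are labelled exploratory, the sample size was set by feasibility, and limited power is acknowledged. All of this stands and limits the consequence. Listing baseline as a repeated observation is ordinary longitudinal modelling, and the contrast is not biased.

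A reader might go further and infer from the phrase about group differences across the three observations that the test is a group effect pooled over all visits, or an omnibus two-degree-of-freedom group-by-time test. At ρ = .50, with d = 0.7 at both later visits, those would have about 55% and 60% power. That is 20 to 25 points below the adjusted contrast, and the pooled effect would shrink to 0.7 × 2/3 = 0.47 SD. The document does not support this reading. It names neither test, and the same section gives differential change from baseline to follow-up as its effect.

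**Conclusion.** The point holds as a loss of efficiency and a power figure that does not match the named contrast. It is not an invalid test. On the plan's own inputs, the baseline-to-week-24 change has about 70% power instead of 80%, and adjusting for baseline brings it to about 81%. The gain is about 10 points at correlation .50, ranging from 16 points at .30 to 4 at .70.

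These figures rest on continuous outcomes, equal variances, a common correlation and 20 completers per arm. They do not carry over to urine toxicology results or time to relapse. They carry over to pill-count adherence, the article's worked example, only if the first count precedes randomisation. The article places that count within a week of training at the initial visit and does not say on which side of randomisation it falls.

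**What to change.** Add to Statistical Analyses, for continuous measures with a pre-randomisation value (for example Timeline Followback percent days abstinent, ASI composites, PHQ-9, OASIS and SF-12):

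*The random effects model is fitted to the post-randomisation visits with the baseline value of the same measure as a covariate or, alternatively, keeps baseline as an outcome with the two arms' baseline means constrained to be equal. The treatment effect is the between-group contrast at week 24, with the week-12 contrast reported beside it.*

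For pill-count adherence, state whether the first count is taken before randomisation, and apply the adjustment only if it is. Restate the power sentence for the contrast actually used: about 81% at d=.7 with baseline adjustment, or about 70% if the change score is kept.

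The cost is a sentence or two and a different model statement. No visit, measurement or participant is added, and about one degree of freedom is used. The article describes data collection as ongoing, so at the time of writing the model could still be fixed before analysis.

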### Sample Size

Determination of sample size (proposed n=25 per group) was guided by feasibility and appropriateness to achieve pilot study objectives rather than by statistical power estimates [44,45]. Pilot studies play an important role in providing information for the planning and justification of RCTs in terms of feasibility of intervention protocols and recruitment strategies, feasibility and comprehensiveness of data management and analysis procedures, and exploration of potential effect sizes [46-48]. We anticipated that the sample size (N=50) would provide representativeness of a diversity of HIV-infected substance user characteristics for examining intervention feasibility and produce data characteristics/distributions appropriate to examining data- and analysis-related procedures, variability, and potential effect sizes.

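### For the change contrast as worded, the detectable effect of d=.7 is the no-attrition figure; after the 20% loss it is about 0.77 to 0.80 unless the analysis is baseline-adjusted

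*Protocol article*

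**What the plan says.** The power statement stands in the protocol article under Statistical Analyses. With 25 in each group, the design "should allow detection of an effect size of approximately d=.7 in differential change in outcomes from baseline to follow-up". The inputs given for this are a correlation of 0.50 between occasions, a loss of at most 20% of participants, and "power=.80, one-tailed alpha=.05". The same paragraph converts the effect to "a differential change of about 19 points on the ART adherence composite score", using a standard deviation of about 27, averaged over time and pooled over groups, from an earlier CBT trial.

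The analysis named there is a random effects regression of "group differences across the repeated observations (baseline, treatment end, and follow-up"). Baseline is thus one of the repeated observations. Covariates are described as characteristics on which the groups differ at admission. The section on substance use adds the drug use severity composite of the Addiction Severity Index as a covariate. Neither place says that every outcome will be adjusted for its own baseline value.

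The Sample Size section says: "Determination of sample size (proposed n=25 per group) was guided by feasibility", and states that power estimates did not determine it.

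**The concern.** The sentence claims to have allowed for attrition, yet the simplest calculation for the contrast it names returns .7 with nobody lost. If that contrast is the one analysed, the plan's only power figure is too favourable.

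The number of participants does not depend on it. What is at stake is interpretation. The Aims section speaks of testing efficacy and states superiority hypotheses, and the Limitations section makes a larger trial follow if those hypotheses are supported. A null result on ART adherence would be read against 80% power for 19 points, when the contrast as worded has nearer 70%.

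**Working it through.** **Inputs, all from Statistical Analyses:** 25 per group; correlation r = 0.50; attrition up to 20%, so 25 × 0.80 = 20 per group; power 0.80; one-tailed alpha 0.05; SD 27.

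**Formula.** Detectable d = (1.645 + 0.842) × √(2f/n), in units of the SD of one measurement. The variance factor f depends on the contrast:
- Unadjusted change from baseline to follow-up: f = 2(1 − r) = 1. At r = 0.50 a change has the same SD as a single measurement.
- Follow-up adjusted for baseline: f = 1 − r² = 0.75.
- Mean of the two post-baseline visits minus baseline: f = (1 + r)/2 + 1 − 2r = 0.75.

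**Step 1: the plan's own figure.** Unadjusted change, n = 25, no loss: 2.487 × √(2/25) = 0.703 (0.713 with the t distribution). Also, 0.703 × 27 = 19.0 and 0.7 × 27 = 18.9. Both the printed .7 and the printed 19 points are matched, but with no attrition.

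**Step 2: the same contrast with the stated loss, completers only.** n = 20: 2.487 × √(2/20) = 0.786 (t: 0.801), which is 21.2 to 21.6 points. Power at d = .7: 0.7/√(2/20) − 1.645 = 0.569, giving 71.5% (t: 70.2%).

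**Step 3: the same contrast in a mixed model that keeps the dropouts' baselines.** With 25 baselines and 20 follow-ups per arm, the variance of the estimated mean change per arm is (1 − r²)/20 + (1 − r)²/25 = 0.0375 + 0.0100 = 0.0475. Then d = 2.487 × √(2 × 0.0475) = 0.766, or 20.7 points, and power at d = .7 is 73.4%. If dropouts also contribute treatment-end data, d is 0.76 and power about 74%.

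**Step 4: contrasts under which the printed figure holds.** With f = 0.75 and n = 20: 2.487 × √(1.5/20) = 0.681 (t: 0.694 for baseline adjustment, 0.693 for the mean of two visits). Power at d = .7 is 81.9% (t: about 81%). A mixed model with baseline means constrained equal between arms gives 0.67 to 0.68 and 82 to 83%.

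| Contrast, one-tailed 5% | n per group | Detectable d | Power at d = .7 |
|---|---|---|---|
| Unadjusted change, no loss | 25 | 0.70–0.71 | 79–80% |
| Unadjusted change, completers | 20 | 0.79–0.80 | 70–72% |
| Unadjusted change, all baselines kept | 25 / 20 | 0.77 | 73% |
| Baseline-adjusted | 20 | 0.68–0.69 | 81–82% |
| Mean of two post visits minus baseline | 20 | 0.68–0.69 | 81–82% |

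**The case against.** The strongest reply is that the article does not give its power formula, and that two reasonable contrasts reproduce .7 at 20 per group with every stated input. Under randomisation a baseline-adjusted comparison estimates the same treatment effect as a comparison of changes, so the sponsor may well have had it in mind. A condensed article may leave the formula to a fuller document. This stands, and it rules out the flat claim that the printed figure is wrong or that attrition was forgotten. A reader might infer that from Step 1, but the match at 25 per group does not show how the figure was obtained. What remains is that the article words the contrast as change between two occasions and treats baseline as an outcome, and under that wording the figure fails.

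Second, the figure is called approximate and the attrition is an upper limit. At 10% loss (22.5 per group) the unadjusted contrast gives 2.487 × √(2/22.5) = 0.74. That is fair, but the sentence claims 80% power while "allowing attrition of up to 20" percent, so the full loss is the case to check.

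Third, the consequences are limited. The sample size rests on feasibility, the regressions are called exploratory, and the Limitations section concedes that power is limited. This lowers the priority but does not make the figure fit the wording.

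A reader might also infer that the plan discards the week 4 and 8 data, since the model sentence names only three occasions. The text does not support this: the next sentence allows further repeated observations for some measures.

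**Conclusion.** The point holds conditionally. For an unadjusted change contrast, d of about .7 and 19 points describe the trial without attrition. At the full 20% loss the detectable effect is about 0.77 (mixed model, all baselines kept) to 0.80 (completers only), which is about 21 to 22 points, and power at d = .7 is about 70 to 73%. For a baseline-adjusted contrast, or one against the mean of both post-baseline visits, the printed figure stands. The text specifies neither.

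These results assume the plan's own r of 0.50 and SD of 27, equal variance over time, and 20 per group remaining. They keep the one-tailed 5% test, which the plan states openly for directional hypotheses and which is not at issue here. The conversion of .7 to 19 points is correct. Priority is moderate.

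**What to change.** Preferred: state under Statistical Analyses that each outcome will be compared in a mixed model with its own baseline value as a covariate, or with baseline means constrained equal between arms, and that the detectable effect refers to this comparison. The printed d of about .7 is then true after 20% attrition, with power of about 81 to 82%.

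Alternative, if the unadjusted change contrast is kept: restate the detectable effect as about .8 (21 to 22 points) at 20% attrition, or keep d = .7 and give its power as about 70 to 73%.

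Both options are changes of wording and model specification. The baseline values are already collected, and no participants, visits or change to the 25 per group are needed. The only cost of the alternative is a less favourable printed figure.

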#### Text CRAVE

In addition to the programmed delivery of daily messages, participants had the option to send a CRAVE text that generated programmed feedback in the form of advice or suggestions when they experienced a craving [50]. In this regard, the TXT-CBT intervention provided a near real-time medium to facilitate the use of social support and feedback, key elements of CBT model, for coping with the craving without using. To keep the messages novel and nonrepetitive, participants rarely (if ever) received the exact same message more than once throughout the duration of the study.

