### Primary Outcomes

#### Substance Use

Substance use was assessed using urine drug screens, the Addiction Severity Index, and the Timeline Followback (TLFB) method. Urine drug screens were collected at baseline and weeks 4, 8, 12, and 24 using temperature-controlled test cups. A US Food and Drug Administration–approved one-step, rapid dip drug test is used (CLIAwaived Inc). The urine drug screens tested for the presence of amphetamines, benzodiazepines, methadone, cocaine, methamphetamine, barbiturates, oxycotin, opiates, and marijuana.

The Addiction Severity Index [51], collected at baseline, treatment end, and follow-up, was used to assess psychiatric and substance use disorder severity and other domains of functioning. Composite scores (alcohol and drug, psychiatric, legal, family, and employment) will be contrasted between groups at baseline to evaluate the effectiveness of randomization. Drug use severity composite scores will be used as a covariate in the analysis of differential treatment effects on outcomes.

The TLFB, a calendar-assisted structured interview [52] with demonstrated validity in substance treatment samples [53], was used to assess drug use in the preceding 90-day period at baseline and follow-up and preceding 30-day drug use at weeks 4, 8, and 12. The TLFB was used to calculate self-report substance outcome variables including percent days abstinent as reported in Project MATCH [54]. Time to first relapse was also evaluated using the TLFB. As in prior work [55], relapse was defined as the first drug use following 7 consecutive days of abstinence after the initiation of treatment.

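### Aim 3 lists no measure of cravings or social support, and self-efficacy is first re-measured at week 12, too late to precede retention or on-treatment drug use

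*Protocol article*

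**What the plan says.** In the Aims section, the third hypothesis says that TXT-CBT acts on recognised psychological mechanisms of CBT. It predicts that "reductions in negative affect and cravings and increases in self-efficacy and social support would be positively associated with retention in TXT-CBT", and that these changes would be "inversely related to substance use during and after treatment".

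Under Statistical Analyses, the one analysis named specifically for this aim is "correlations between changes in self-efficacy (Drug-Taking Confidence Questionniare) and treatment retention and substance use during and after treatment". The same section plans random effects regression of group differences for the measures under each aim.

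Table 1 schedules the Drug-Taking Confidence Questionnaire at baseline, week 12 and follow-up (week 24), and not at weeks 4 or 8. It schedules the PHQ-9 and OASIS at baseline, weeks 4, 8 and 12, and follow-up. Neither Table 1 nor the outcome sections list a craving scale or a social support scale.

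The Discussion describes the process analyses as exploratory. It also expects that known active ingredients of face-to-face CBT, with self-efficacy as its example, will explain part of any benefit. The Strengths paragraph counts the study of mechanisms as one of the trial's merits.

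**The concern.** There are two separate faults.

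First, the hypothesis and the listed measures do not match. A prediction about cravings and social support cannot be examined if neither is recorded in a form that yields a change score in both arms.

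Second, a mechanism has to change before the outcome it is meant to explain. The first available self-efficacy change ends at week 12, when the 12-week programme also ends. A participant who stopped using drugs early may be more confident at week 12 for that reason alone. A correlation between that change and on-treatment use, or retention in the programme, would look the same whichever came first.

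What is at stake is the reading of aim 3, one of three specific aims. A correlation in the expected direction could be reported as evidence of how TXT-CBT works when the schedule does not allow that inference.

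**Working it through.** **1. Hypothesised mechanisms against listed measures**

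| Mechanism | Listed measure | Times |
|---|---|---|
| Negative affect | PHQ-9, OASIS | baseline, weeks 4, 8, 12, 24 |
| Self-efficacy | Drug-Taking Confidence Questionnaire | baseline, weeks 12, 24 |
| Cravings | none | – |
| Social support | none | – |

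Two of four have a measure. The nearest substitutes do not fill the gap:
- Cravings: in the Text CRAVE section, "participants had the option to send a CRAVE text that generated programmed feedback". This is optional and exists only in the TXT-CBT arm. In the self-efficacy questionnaire, participants "rated confidence in resisting the urge to drink heavily or use a specific drug", which is confidence, not craving intensity.
- Social support: the Addiction Severity Index has a family composite, but the use stated for it is a check at baseline: "Composite scores (alcohol and drug, psychiatric, legal, family, and employment) will be contrasted between groups at baseline".

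**2. Time order of the named correlation**

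Count days from the start of treatment, with week 12 = day 84 and week 24 = day 168, and assume visits on schedule.
- The first self-efficacy change score runs from day 0 to day 84.
- Retention in a 12-week programme is complete at day 84, so the change does not precede it.
- On-treatment use comes from urine at weeks 4, 8 and 12 and from 30-day Timeline Followback recall at the same visits. The last recall window closes on day 84. All of it lies before the week-12 questionnaire or coincides with it.
- Post-treatment use comes from urine at week 24 and a 90-day recall at follow-up. That window opens on day 168 − 90 = 78, which is week 78/7 = 11.1. It overlaps treatment by 84 − 78 = 6 days and otherwise follows the week-12 questionnaire. The order is right once those days are removed.
- If change were instead taken from baseline to week 24, post-treatment use would also fall before the end of the change interval. The article does not say which change is meant.

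Time order is therefore wrong for two of the three targets (retention and on-treatment use) and right for the third if change to week 12 is used. PHQ-9 and OASIS change from baseline to week 4 precedes use and retention after week 4.

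**3. Precision**

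The article gives no figure for aim 3. Its only computed figure is a detectable d of about 0.7 for group differences (power .80, one-tailed .05, correlation 0.50 over time, up to 20% attrition). With 25 × 0.8 = 20 per group and baseline adjustment, d = √(1 − 0.5²) × (1.645 + 0.842) × √(2/20) = 0.866 × 2.487 × 0.316 = 0.68, which agrees. A plain change score with 20 per group gives 2.487 × 0.316 = 0.79. The article does not say which was used, and the present point does not depend on it.

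With the same alpha and power, the detectable correlation is r = tanh[(1.645 + 0.842)/√(n − 3)]:
- n = 20 (one arm after 20% attrition): tanh(2.487/4.123) = 0.54
- n = 25 (one arm, no attrition): tanh(2.487/4.690) = 0.49
- n = 40 (both arms after attrition): tanh(2.487/6.083) = 0.39
- n = 50 (both arms, no attrition): tanh(2.487/6.856) = 0.35

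**The case against.** The strongest defence has four parts.

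*The wording is modest.* The specific predictions are stated as associations, and the process work is called exploratory. A correlation has no direction, so the planned analysis can be computed and reported. This stands, and it makes the fault one of interpretation. It does not cover the Discussion, which expects self-efficacy to account for part of the treatment effect.

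*The article is condensed.* Table 1 presents itself as a list of key variables, so a fuller protocol may hold craving and social support scales. That is possible, and the fix allows for it. But the article describes each secondary instrument separately, and these two are hypothesis variables.

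*The plan has more than one correlation.* "Analyses for aim 3 will include correlations between changes in self-efficacy" is not an exhaustive list, and the random effects models already cover arm differences for each aim's measures. This stands. A reader might infer that the plan never examines whether TXT-CBT moves the mechanisms; the article does not support that.

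*Retention is not defined.* A reader might infer that everyone with a week-12 score was retained, so that retention hardly varies among them. Texting STOP does disenrol a participant from the study, but others could stop engaging and still attend week 12, and message exposure is recorded separately. The article gives no figure for this, so the point rests on timing alone.

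**Conclusion.** The point holds in a limited form. Cravings and social support, two of four hypothesised mechanisms, have no listed measure. Two of the three stated self-efficacy correlations cannot show that self-efficacy came first, so they do not support the mechanism expectation in the Discussion.

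A reader might go further and infer that aim 3 cannot be tested at all. The article does not support that: negative affect is measured at every visit from baseline, and baseline-to-week-12 self-efficacy change does precede post-treatment use.

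Nor is the precision limit uniformly severe. The detectable r of 0.54 applies to a single-arm analysis of 20. Only the retention prediction is clearly confined to TXT-CBT; a correlation pooled over both arms could detect about 0.39 with 40.

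The conclusion assumes that Table 1 and the outcome sections give the full set of relevant instruments, that visits fall on schedule, and that retention means retention in the 12-week programme.

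**What to change.** All of this can be done in the analysis wording, with data already being collected:
- Limit the third hypothesis to negative affect and self-efficacy, unless the full protocol holds craving and social support instruments; if it does, name them and their schedule.
- Relate self-efficacy change from baseline to week 12 only to use after week 12, namely the week-24 urine screen and the Timeline Followback days after week 12, leaving out the roughly 6 days of recall that fall within treatment. Adjust for arm and for use at the end of treatment.
- Relate PHQ-9 and OASIS change from baseline to week 4 to drug use and retention after week 4.
- If the self-efficacy correlations with retention and on-treatment use are kept, report them as descriptive and without direction.

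Adding self-efficacy items at weeks 4 and 8 is not worthwhile now. Data collection was due to end in July 2016, so only participants who had not yet passed those visits would supply them.

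The cost is a narrower hypothesis and fewer outcome data points for self-efficacy. The limited precision remains and should be stated with the results.
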